### Study assessments

Preoperative assessments will include a patient reported questionnaire examining pain and function (OKS), activity level and healthcare resource use. In addition, the American Knee Society Score (AKSS), a clinical assessment of range of motion and function of the knee, will be carried out. Routine preoperative X-rays will also be collected.

Operative details will be recorded and routine postoperative X-rays collected.

Patients will be required to attend a clinic appointment for the AKSS assessment at 2 months, 1 and 5 years post operation. The first two visits will coincide with routine hospital follow-up visits for these knee replacement procedures.

A postal questionnaire (containing the OKS, UCLA, HAAS, EQ-5D, Lund, healthcare and patient resource use) will also be sent out at years 1 to year 5 post randomisation. Additional clinical and postal questionnaire assessments are planned for years 7 and 10 subject to funding. The components of follow-up are shown in Table 1.

**Table 1 T1:** Components of follow-up time points

	**Pre**	**2 months**	**1 year**	**2 years**	**3 years**	**4 years**	**5 years**	**7 years**	**10 years**
OKS (self-report function)	*▲*	*○*	*○*	*○*	*○*	*○*	*○*	*○*	*○*
AKSS (clinical exam)	*▲*	*▲*	*▲*				*▲*		*▲*
UCLA (self-report activity)	*▲*	*○*	*○*	*○*	*○*	*○*	*○*	*○*	*○*
High Activity Arthroplasty Score	*▲*	*○*	*○*	*○*	*○*	*○*	*○*	*○*	*○*
X-rays	*▲*	*▲**					*▲*		*▲*
EQ-5D	*▲*	*○*	*○*	*○*	*○*	*○*	*○*	*○*	*○*
Lund (patient satisfaction)		*○*	*○*	*○*	*○*	*○*	*○*	*○*	*○*
Complications		*▲*	*▲*	*○*	*○*	*○*	*▲*	*○*	*▲*
Healthcare and patient resource use	*▲*	*○*	*○*	*○*	*○*	*○*	*○*	*○*	*○*

*▲* = Collected at clinic visit *○* = Postal Questionnaires * = Immediately Post Op.

Due to the variation in waiting times for surgery at participating sites, it is possible that a small number of participants may receive their 1 year follow-up questionnaire (which is sent post randomisation) at a time point much earlier than 1 year post surgery when the clinical assessment is carried out. These patients will have their 1 year assessment too early in their recovery for the results to be valid and there will be great variation in follow-up time. In cases where there is more than 12 weeks between randomisation of a patient to treatment and their operation date, an additional OKS will be administered at the clinical assessment 1 year post surgery.

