### Statistical analysis

Principle analyses will be based on an ‘intention to treat’ basis where participants will be analysed according to the allocated group using all available participant data. Statistical significance will be judged at the two-sided 5% level with corresponding 95% confidence interval presented. A short summary of the proposed analyses is given below. Further details of the planned statistical analyses are contained in the Statistical Analysis Plan, which will be finalised, prior to the unblinding of data.

Three sets of analyses are planned, based on the anticipated follow-up period. By 2 years, all patients are anticipated to have received surgery. Analyses are planned at 1 year post operation (3 years into the trial), at 5 years randomisation (7 years into the trial) and 10 years post randomisation (12 years into the trial).

Under the principal analysis of the primary outcome, the OKS score will be compared at each assessment point alone (multiple linear regression analysis adjusted for minimisation factors). The impact of adjusting for delivery unit will be explored using multilevel modelling. A stratified analysis (and associated interaction effect) will be performed to allow for a difference between expertise versus equipoise delivery of the treatments and the potential impact upon the comparison. Secondary analyses will explore the potential impact of missing data and alternative analytic approaches. In addition to the analyses planned once 5 and 10 year follow-up has matured, a complementary analysis will also compare the OKS over all assessments (the follow-up period) using multilevel modelling to allow for repeated measurements for participants. One secondary analysis, using an external comparative cohort, will also evaluate whether trial patients are representative, in terms of age, patient demographics and operative findings, of patients undergoing UKR and TKR in the general population.

Secondary outcomes will be analysed in a similar manner adjusting for minimisation factors where appropriate within a generalised linear models framework. Confidential interim analysis will be performed as requested by the Data Monitoring Committee.

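### For patients who wait more than 12 weeks for surgery, only the OKS is repeated at 1 year after operation, so the 1-year UCLA, HAAS and Lund scores are mistimed or missing

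*Protocol article*

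**What the plan says.** The Study assessments section of the Protocol article uses two clocks. The clinic visits run from surgery: "Patients will be required to attend a clinic appointment for the AKSS assessment at 2 months, 1 and 5 years post operation". The postal form runs from randomisation, goes out annually for five years, and bundles several instruments: "A postal questionnaire (containing the OKS, UCLA, HAAS, EQ-5D, Lund, healthcare and patient resource use) will also be sent out at years 1 to year".

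The article sees that the clocks can drift apart. Because waiting times vary between sites, "it is possible that a small number of participants may receive their 1 year follow-up questionnaire" well before they are a year past surgery. Its judgement on such forms is: "These patients will have their 1 year assessment too early in their recovery for the results to be valid". The remedy is triggered by a waiting time, "In cases where there is more than 12 weeks between randomisation of a patient to treatment and their operation date", and consists of one instrument: "an additional OKS will be administered at the clinical assessment 1 year post surgery".

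Table 1 marks UCLA, HAAS and Lund at 1 year as postal only. At that time point the clinic visit collects the AKSS and complications.

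The Statistical analysis section places the first set of analyses at 1 year after operation. On the other outcomes it says: "Secondary outcomes will be analysed in a similar manner adjusting for minimisation factors where appropriate".

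**The concern.** The reason given for distrusting the early form is incomplete recovery. That reason is not specific to the OKS. Activity level (UCLA, HAAS) and satisfaction (Lund) also depend on how far the patient has recovered, and they are on the same sheet, completed on the same day. The article identifies a timing problem with the 1-year assessment and corrects one instrument.

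At stake is the set of activity and satisfaction results that would accompany the OKS in the 1-year analysis. In late-operated patients those scores would describe an earlier stage of recovery than the repeat OKS and the AKSS beside them, or they would be absent. This is a data-collection matter. An analysis plan can exclude or flag an early score, but it cannot supply a 1-year post-operative score that nobody collected.

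**Working it through.** The point rests on the text, and the article gives no figure for it beyond the 12-week trigger. The sample size is not involved.

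**Which instruments are affected**

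| Instrument at 1 year | How collected (Table 1) | Clock | Repeated if wait exceeds 12 weeks? |
|---|---|---|---|
| OKS | post | randomisation | yes, at the visit 1 year after surgery |
| UCLA | post | randomisation | no |
| HAAS | post | randomisation | no |
| Lund | post | randomisation | no |
| EQ-5D, resource use | post | randomisation | no |
| AKSS | clinic | operation | not needed |

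EQ-5D and resource use are set aside. They feed QALYs and costs, which can properly run from randomisation.

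**Timing of the unrepeated scores**

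Inputs: a form due 52 weeks after randomisation, and a wait of *w* weeks from randomisation to operation. Time since surgery at the 1-year form is 52 − *w*. At the next annual form it is 104 − *w*. The 12-week row is the article's trigger; the other waits are illustrative.

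| Wait *w* (weeks) | 1-year form, weeks after surgery | 2-year form, weeks after surgery | Repeat OKS and AKSS, weeks after surgery |
|---|---|---|---|
| 12 (trigger boundary) | 52 − 12 = 40 | 104 − 12 = 92 | AKSS 52; no repeat OKS |
| 13 | 39 | 91 | 52 |
| 16 | 36 | 88 | 52 |
| 26 | 26 | 78 | 52 |

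Every patient who triggers the repeat therefore has 1-year UCLA, HAAS and Lund scores from less than 40 weeks after surgery. The next scheduled form does not fill the gap: at a 26-week wait, the two forms lie 26 weeks either side of the 52-week mark.

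**How many patients**

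The article gives no count and no share, only that the number is expected to be small. Assumed shares of the 500 patients give:

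- 5%: 0.05 × 500 = 25
- 10%: 0.10 × 500 = 50
- 20%: 0.20 × 500 = 100

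The article's own expectation points to the lower end of this range.

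**Who can still be reached**

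The 1-year post-surgery visit falls 52 + *w* weeks after randomisation, so more than 52 + 12 = 64 weeks for anyone who triggers the repeat. Trial status reports that recruitment opened in January 2010, that 478 patients were randomised by May 2013, and that recruitment was to run to September 2013. The visit has passed for many earlier recruits and is still ahead for later ones.

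**The case against.** The best defence is that repeating only the primary outcome is a reasonable choice about burden. It protects the OKS in a small group at a time point that is not primary. The Primary outcome measure section puts the primary analysis at 5 years and mentions the 1-year look only as an early analysis of the OKS. UCLA, HAAS and Lund are collected again every year from 2 to 5. This limits the importance of the point but does not remove the gap: the Statistical analysis section schedules a 1-year post-operation analysis and treats secondary outcomes similarly.

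A second defence is that the judgement on validity is followed at once by an OKS remedy, and so may have been meant for the OKS alone. The sentence, however, speaks of the 1-year assessment and gives a reason that applies to all the recovery-dependent scores. It is also true that a 13-week wait gives 39 weeks where a 12-week wait, accepted without a repeat, gives 40. Any cut-off has this feature, and the trigger itself is not in question here.

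A third objection is that a repeat would mix time origins: patients with short waits stay on the randomisation clock and the others move to the surgery clock, according to an event after randomisation. That is correct, but it applies equally to the OKS rule the article has already adopted.

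Two stronger readings are tempting and are not supported:

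- *That the trial will analyse scores its own protocol rejects.* The article does not say so. Its commitment to use all available data belongs to the intention-to-treat statement and is not a rule for mistimed forms. Handling may be settled in the analysis plan, which is not shown.
- *That the comparison between arms is biased.* Internal referral in expertise units could lengthen some waits, but the recruiting surgeon may be the TKR or the UKR surgeon, so the delay could fall on either arm. Delivery unit is a minimisation factor, which helps balance differences in waiting between sites. The Background reports a belief that UKR gives faster recovery, which could make an early contrast differ from a 52-week one even with equal waits, but nothing in the article quantifies this.

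**Conclusion.** The gap is real and minor. Followed as written, the article provides no UCLA, HAAS or Lund score at 1 year after operation for patients who wait more than 12 weeks. Their data for the 1-year analysis will either come from less than 40 weeks after surgery or be missing, while the repeat OKS and the AKSS stand at 52 weeks.

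The timing follows directly from the two clocks. The number affected is assumed: 25 to 100 of 500 at shares of 5% to 20%, probably near the lower end. No effect on any treatment comparison can be calculated from the article, and no difference between arms is shown. The primary outcome, the 5-year primary analysis and the cost-utility analysis are untouched.

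**What to change.** For patients who waited more than 12 weeks and whose 1-year post-surgery visit is still ahead, give UCLA, HAAS and Lund together with the repeat OKS, and use those scores in the 1-year post-operation analysis.

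For patients already past that visit, record the early UCLA, HAAS and Lund scores as mistimed and run a sensitivity analysis that excludes them.

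Leave EQ-5D and resource use timed from randomisation.

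The cost is a few minutes of extra patient time, for a minority of patients, at an existing visit where an additional questionnaire is already given. Two drawbacks should be stated with the results. The three scores would take on the mixed time origin already accepted for the OKS. And because recruitment is well advanced, repeat scores would exist only for later patients, so the late-operated group would be split by calendar time.

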### Randomisation procedures

Randomisation will occur using a web-based randomisation service at the Centre for Healthcare Randomised Controlled Trials (CHaRT), Health Services Research Unit, University of Aberdeen.

The minimisation algorithm will incorporate gender, age and baseline OKS and ‘delivery unit’. A delivery unit is either an ‘equipoise surgeon’ or a pair of ‘expertise surgeons’ with complementary expertise (that is, one TKR-focused and one UKR-focused).

This factor is included to ensure balance is maintained for individual equipoise surgeons and more generally by centre. Participating surgeons will be discouraged from changing practice during the course of the trial. Within a centre there may be a mixture of delivery unit types. Local recruitment officers at each site will undertake the randomisation. The randomised treatment will be recorded in the patient’s hospital notes and study notes and the surgeon will be notified. If the allocated operation is not provided by the recruiting surgeon (for example, they are an ‘expertise surgeon’ who provide the other operation), an ‘internal referral’ to their delivery unit colleague will be initiated. A standard letter informing the admissions department/care-pathway coordinators will be sent. Local study staff will oversee this referral. Patients’ GPs will also be notified at this time.

### Interventions

TOPKAT will be pragmatic in terms of implant selection for the knee replacement operation. Providing the above conditions are met, surgeons will be entirely free to use an implant of their choice or will use the current implants used at their institution. Implant type used on each patient will be recorded.

#### Total knee replacement

A total knee replacement involves all surfaces of the knee being replaced. The procedure involves excising both diseased and normal femoral condyles, the tibial plateau and often the patella. This is done through a large skin incision which provides easy access to the knee joint. Each component will be replaced with an artificial implant, which may be cemented in position.

#### Partial knee replacement

A partial knee replacement or UKR involves only the diseased area of the joint being replaced. The healthy compartment of the knee is retained and artificial implants are inserted in place of the diseased area. This is done via a minimally invasive surgical procedure.

### Safety

The TOPKAT trial involves routine knee replacement surgery for medial compartmental osteoarthritis. There are no additional risks to patients. They will undergo knee replacement as per standard management regime. The benefits will be to future patients although involvement in the trial with specific outcome measurement may be perceived as a benefit by some patients. Patients will be informed of the standard risks associated with anaesthetic and knee replacement operations.

Possible (expected) complications and consequences are:

•All substantive surgical procedures (including knee replacement) whether primary or revision procedures carry a risk of anaesthesia-related problems, death, morbidity including wound infection, bleeding intra- and postoperatively, thrombo-embolic complications and complications secondary to existing co-morbidity, for example, ischaemic heart disease.

•Specific complications following knee replacement procedures include loosening of components - tibia/femur/both, dislocation of knee/bearing, superficial and deep infection, unexplained knee pain, knee stiffness, haematoma, mechanical failure of replacement, periprosthetic fracture. These complications may result in the need for further surgery such as revision operations, arthroscopy, washout, manipulation under anaesthetic, debridement (open), aspiration, above knee amputation, patella resurfacing.

For the purpose of TOPKAT, a serious adverse event (SAE) is defined as any adverse event during the course of the study resulting from the administration of any of the research procedures required by the protocol that:

•Results in death,

•Is life-threatening†,

•Requires inpatient hospitalisation or prolongation of existing hospitalisation,

•Results in persistent or significant disability/incapacity, or

•Other important medical events*

† The term ‘life-threatening’ in the definition of ‘serious’ refers to an event in which the participant was at risk of death at the time of the event; it does not refer to an event which hypothetically might have caused death if it were more severe.

*Other events that may not result in death, are not life-threatening, or do not require hospitalisation, may be considered a SAE when, based upon appropriate medical judgement, the event may jeopardise the participant and may require medical or surgical intervention to prevent one of the outcomes listed above.

All SAEs will be notified to the appropriate authorities (Research Ethics Committee (REC) and Sponsor) within the timelines specified.

When the web-based SAE form is completed detailing any possible related and unexpected SAEs, the Chief Investigator (CI) or deputy will be notified automatically. If, in the opinion of the local surgeon and the CI, the event is confirmed as being related and unexpected (that is, not listed as a possible expected occurrence), the CI will submit a report to the main REC and the study sponsors within 15 days of the CI becoming aware of it.

The reporting procedures for all study-related adverse events are detailed in accordance with the guidance from the National Research Ethics Service (NRES).

### Reporting of postsurgical complications

The annual postal self-report questionnaires will ask patients if they have been admitted to hospital at any point over the last 12 months. Any readmissions will be followed up by the trial coordinator in Oxford who will contact the recruitment officers at the patient’s hospital and ask them to collect further information about the readmission event. Details of any readmissions that are study-related (that is, result from administration of any of the procedures required by the trial protocol) and are expected (that is, listed as a possible expected occurrence) will be collected.

At the routine follow-up clinical visits, patients will also be asked if they have experienced any complications related to their study knee since their last scheduled TOPKAT visit, which resulted in them visiting a healthcare practitioner. This information will be recorded.

### Statistics and analysis

#### Sample size

The sample size for the trial (250 in each arm, 500 overall) has been based on a number of considerations, drawing on what previous research has suggested is both plausible and the likely size of difference that is clinically significant.

#### Primary outcome - OKS score

Table 2 shows the number of subjects required in each randomised group to give either 80% or 90% power to detect differences in the OKS of 2.0, 3.0 and 4.0, at either the two-sided 1% or 5% significance level and with SD of 8.0, 9.0 or 10.0.

**Table 2 T2:** Sample size scenarios

**Number in each group**		**Mean difference in OKS**					
		**2.0**		**3.0**		**4.0**	
**Power**	**SD**	**1% sig level**	**5% sig level**	**1% sig level**	**5% sig level**	**1% sig level**	**5% sig level**
90	8.0	480	340	215	150	120	85
	9.0	600	430	270	190	150	110
	10.0	740	520	330	235	190	130
80	8.0	375	250	170	110	100	60
	9.0	470	320	210	140	120	80
	10.0	590	390	260	175	150	100

The minimal clinically significant difference of the OKS is judged to be 2.0, and the likely SD of the OKS is 8.0 [46]. A sample size of 500 patients (250 in each group) would provide 80% power to detect a difference of 2.0 at 5% (two-sided) significance level. Since it is possible that the SD of the OKS could be >8.0 [13], this size of sample would allow for the detection of a difference of 3.0 in OKS with a SD of 10.0 at 5% (two-sided) significance level and 90% power and also a difference of 3.0 at 1% (two-sided) significance level with 80% power.

Indeed, almost all of the above scenarios are detectable if the difference in OKS is 3.0 rather than 2.0. This difference of 3.0 in the OKS is equivalent to a typical category change in the American Knee Society Score [40]. Furthermore, a difference in the OKS of 4.0 would, with 250 patients per group allow for some subgroup analyses. As previous research (the Bristol RCT) suggests that the difference between the groups is indeed likely to be >2.0 [6], a sample size of 250 in each arm would allow for some non-response yet still detect differences. As the statistical analysis will adjust for the baseline value and account for the surgical delivery unit this will likely increase precision. Offsetting this will be any missing data which would have the reverse impact.

#### Re-operation (including revision) of the device

UKR may be associated with higher re-operation rates, including revision. The re-operation rate after TKR is anticipated to be approximately 5% at 5 years [47]. A sample size of 250 patients per group would give 80% power at *P* <0.05 to detect an increase to 12% (compared to just under 5%), and 90% power at *P* <0.05 to detect an increase to 14%. Analysis based on the time to re-operation using survival analysis will likely be more than sufficient.

### Statistical analysis

Principle analyses will be based on an ‘intention to treat’ basis where participants will be analysed according to the allocated group using all available participant data. Statistical significance will be judged at the two-sided 5% level with corresponding 95% confidence interval presented. A short summary of the proposed analyses is given below. Further details of the planned statistical analyses are contained in the Statistical Analysis Plan, which will be finalised, prior to the unblinding of data.

Three sets of analyses are planned, based on the anticipated follow-up period. By 2 years, all patients are anticipated to have received surgery. Analyses are planned at 1 year post operation (3 years into the trial), at 5 years randomisation (7 years into the trial) and 10 years post randomisation (12 years into the trial).

Under the principal analysis of the primary outcome, the OKS score will be compared at each assessment point alone (multiple linear regression analysis adjusted for minimisation factors). The impact of adjusting for delivery unit will be explored using multilevel modelling. A stratified analysis (and associated interaction effect) will be performed to allow for a difference between expertise versus equipoise delivery of the treatments and the potential impact upon the comparison. Secondary analyses will explore the potential impact of missing data and alternative analytic approaches. In addition to the analyses planned once 5 and 10 year follow-up has matured, a complementary analysis will also compare the OKS over all assessments (the follow-up period) using multilevel modelling to allow for repeated measurements for participants. One secondary analysis, using an external comparative cohort, will also evaluate whether trial patients are representative, in terms of age, patient demographics and operative findings, of patients undergoing UKR and TKR in the general population.

Secondary outcomes will be analysed in a similar manner adjusting for minimisation factors where appropriate within a generalised linear models framework. Confidential interim analysis will be performed as requested by the Data Monitoring Committee.

For the health economic evaluation within-trial cost-effectiveness will be assessed at 5 years (and at 10 years - subject to additional funding). Costs and QALYs in each trial arm will be expressed using means and standard deviations. Incremental analysis will be performed. If appropriate, results will be expressed as an incremental cost per QALY gained, with uncertainty around this ratio determined through the use of non-parametric bootstrapping and cost-effectiveness acceptability curves [48,49]. Longer-term extrapolation of results will also be conducted and will use trial data, for example surgical re-operation rates will be projected using a simple parametric model and will be assigned appropriate event costs and utility scores.

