In order to complete the trial by seeking to maximise surgeon participation, an ‘expertise’-based delivery of the intervention will also occur. For this approach there must be a surgeon with expertise in TKR and a surgeon with expertise in UKR in the same centre who will act together as a ‘delivery unit’. Patients recruited to the study who are under the care of such a surgeon (‘expertise surgeon’) will be randomised to one of the two groups and treated by the appropriate surgeon. This ‘expertise’ approach allows for those UKR surgeons who work alongside TKR surgeons to team up and participate in the study. Subsequent surgery may be carried out by a surgeon different to that at the initial consultation. In such cases the patient is internally referred to the other surgeon’s operating list. A study flowchart is detailed in Figure 1. No restriction is made upon the number of delivery units within a centre. A surgeon can only be in one delivery unit, that is, they are either an ‘equipoise surgeon’ or an ‘expertise surgeon’.

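### In expertise delivery units each surgeon operates in one arm only, and neither the principal linear regression nor a delivery-unit intercept allows for this, so the OKS confidence interval is too narrow unless few patients are in such units

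*Protocol article*

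**What the plan says.** The protocol article allows two ways of delivering surgery (Study design). An equipoise surgeon performs both operations. In an expertise unit, a TKR surgeon and a UKR surgeon at one centre form a pair, and patients "will be randomised to one of the two groups and treated by the appropriate surgeon". Randomisation procedures defines the delivery unit as either the single equipoise surgeon or the pair, and lists it with gender, age and baseline OKS as a minimisation factor.

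Statistical analysis makes the principal OKS comparison a linear regression at each assessment, adjusted for the minimisation factors. It adds that "The impact of adjusting for delivery unit will be explored using multilevel modelling", and plans a stratified analysis with an interaction for expertise versus equipoise delivery. On error rates: "Statistical significance will be judged at the two-sided 5% level".

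On sample size (Primary outcome - OKS score): "The minimal clinically significant difference of the OKS is judged to be 2.0", "the likely SD of the OKS is 8.0", and "A sample size of 500 patients (250 in each group) would provide 80% power" for that difference. The section then says: "As the statistical analysis will adjust for the baseline value and account for the surgical delivery unit this will likely increase precision". The one counterweight it names is incomplete data: "Offsetting this will be any missing data which would have the reverse impact". It gives no ICC, cluster size or design effect.

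**The concern.** In an equipoise unit the surgeon is crossed with arm, so that surgeon's general level of results cancels from the comparison. In an expertise unit the surgeon is nested in arm. If one surgeon of the pair tends to get better scores whatever the operation, that difference appears as a treatment effect in that unit. Over many pairs it averages out, so the estimate is not biased by it, but it adds variance that patient-level regression does not count.

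The delivery unit is the wrong level to repair this. A unit intercept, fixed or random, takes the same value in both arms of the pair, so it removes what the two surgeons share and leaves the difference between them.

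The width of the primary confidence interval and the real size of the 5% test are at stake. So is the planned expertise-by-equipoise interaction, because the variance is understated in one stratum and not in the other.

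**Working it through.** **Inputs from the protocol.** Difference 2.0, SD 8.0, 250 per arm, two-sided 5%, 80% power; 500 patients in about 28 hospitals.

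**Assumptions (not in the protocol).** Surgeon ICC ρ = 0.02 to 0.05. Share of patients in expertise units f = 0.5 or 1. Patients per surgeon in one arm m = 9 if each hospital has one unit (500/28/2 = 8.9), or 4.5 if each has two. Baseline-to-outcome correlation r = 0, 0.3 or 0.5.

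**1. The plan's own figure.** n per arm = 2(1.960 + 0.842)² × 8²/2² = 251.2, so 252 against the stated 250. With 250 per arm, SE = 8√(2/250) = 0.7155, and power = Φ(2/0.7155 − 1.960) = Φ(0.835) = 79.8%. The 80% reproduces as a calculation on independent patients, with no allowance for clustering, baseline gain or missing data.

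**2. Variance of the treatment difference.** Relative to what ordinary regression assumes, patient-level variation contributes 1 − ρ, equipoise surgeons cancel, and expertise surgeons contribute f·m·ρ:

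V = 1 + (f·m − 1)ρ

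V exceeds 1 once f is above 1/m: about 11% of patients at m = 9, or 22% at m = 4.5. Below that, regression without a unit term is slightly conservative.

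**3. Type I error and power.** True error of the nominal 5% test = 2[1 − Φ(1.960/√V)]. Power of a test with correct standard errors uses SE = 8√(2(V − r²)/250), which takes baseline adjustment to remove r² of the variance and leave the surgeon component.

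| f | m | ρ | V | Type I error | Power, r = 0 | r = 0.3 | r = 0.5 |
|---|---|---|---|---|---|---|---|
| 0.5 | 4.5 | 0.02 | 1.025 | 5.3% | 79% | 82% | 89% |
| 0.5 | 4.5 | 0.05 | 1.063 | 5.7% | 77% | 81% | 87% |
| 0.5 | 9 | 0.02 | 1.070 | 5.8% | 77% | 81% | 87% |
| 0.5 | 9 | 0.05 | 1.175 | 7.1% | 73% | 77% | 83% |
| 1 | 4.5 | 0.02 | 1.070 | 5.8% | 77% | 81% | 87% |
| 1 | 4.5 | 0.05 | 1.175 | 7.1% | 73% | 77% | 83% |
| 1 | 9 | 0.02 | 1.160 | 6.9% | 74% | 77% | 83% |
| 1 | 9 | 0.05 | 1.400 | 9.8% | 66% | 69% | 74% |

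At f = 0.25, m = 9, ρ = 0.02, V is again 1.025 and the error 5.3%.

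**4. Does a unit term repair it?** A simulation used 28 units with 9 patients per arm in each and 4,000 replicates per scenario (simulation error about √(0.05 × 0.95/4000) = 0.3 points). Type I error:

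| Expertise units | ρ | Ordinary regression | With unit effects |
|---|---|---|---|
| Half | 0.02 | 5.6% | 5.8% |
| Half | 0.05 | 7.1% | 7.5% |
| All | 0.02 | 6.2% | 6.5% |
| All | 0.05 | 9.7% | 9.9% |

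The unit term does not help. It also makes no difference to the conclusion whether the principal regression already contains delivery unit as a minimisation factor, which the text leaves unclear.

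**5. Does baseline adjustment repair the interval?** No. It shrinks the assumed variance but not the surgeon component, so the ratio becomes (V − r²)/(1 − r²). At V = 1.175 and r = 0.5 this is 0.925/0.75 = 1.233, and the error is 7.8% instead of 7.1%.

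**6. Offsets to power.** With no clustering, r = 0.3 alone lifts power to 83% and r = 0.5 to 90%. Loss of 10% of outcomes alone lowers it to 76%.

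**The case against.** The strongest reply is that every adverse figure needs inputs the protocol does not give. A reader might infer that the test exceeds 5% and that the 80% power is not delivered. The documents support neither as a fact. Both unit types are provided for, and the mix is not stated. With equipoise surgeons only, ordinary regression is conservative (3.4% in the simulation at ρ = 0.10). The 28 are hospitals, and Study design sets no limit on delivery units per centre, so 9 patients per surgeon in each arm may be too many. The 80% also leaves out the baseline gain that the sample-size section itself cites, which can cancel a design effect of up to 1 + r², that is 1.09 at r = 0.3 or 1.25 at r = 0.5. All of this stands, and it makes the power claim conditional.

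Second, the article calls its analysis section a summary, and a random-effects structure is commonly left to the SAP. The multilevel model might include a unit-by-treatment term. That is fair as to the exploratory model. But the article does fix the principal model, which is not multilevel, and it names the delivery unit as the clustering level.

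Third, inference could be made conditional on the participating surgeons, and the extra variance would then not arise in this form. In expertise units, however, such an inference compares particular pairs of surgeons, whereas the stated objective is to compare the two operations.

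**Conclusion.** The concern holds in a conditional form. Surgeon is nested in arm in expertise units, the principal analysis ignores this, and a delivery-unit intercept does not capture it. The interval is too narrow if the surgeon ICC is positive and the expertise share is above roughly 1/m. Under an assumed ICC of 0.02 to 0.05 and m of 4.5 to 9, type I error is about 5.3% to 7% with half the patients in expertise units and about 6% to 10% with all of them. The all-expertise figures are an upper bound, because the protocol provides for both types.

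The statement that accounting for delivery unit will probably improve precision is sound for equipoise units only. Net power may fall on either side of 80%: baseline adjustment may offset clustering, and missing data works the other way. The point is of moderate severity and gives no ground for a larger sample.

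**What to change.** - Make the principal OKS model a mixed model with a random effect for operating surgeon and small-sample degrees of freedom. An equivalent form is a delivery-unit intercept plus a unit-by-treatment random effect in expertise units. Defined by allocated arm, this form needs only information known at randomisation and fits the intention-to-treat principle.
- Use the same structure for the expertise-versus-equipoise interaction.
- In the sample-size section, limit the precision statement to baseline adjustment and equipoise units.
- Restate power over stated ranges of surgeon ICC, expertise share, patients per surgeon and baseline correlation, with missing data alongside.

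The cost is a somewhat wider interval: by √V, about 1% to 8% with half the patients in expertise units and 3% to 18% with all of them, over the ranges above. No further patients are needed to correct the standard error. The sponsor should confirm that the operating surgeon is captured, since Study assessments mentions operative details without listing them. The change can be made in the SAP, which is to be finalised before unblinding, with a matching correction to the protocol text.
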